# What is the ideal dose and power output of low-level laser therapy (810 nm) on muscle performance and post-exercise recovery? Study protocol for a double-blind, randomized, placebo-controlled trial

**DOI:** 10.1186/1745-6215-15-69

**Published:** 2014-02-27

**Keywords:** Low-level laser therapy, Skeletal muscle fatigue, Skeletal muscle recovery, Phototherapy parameters, Exercise

## Abstract

**Background:**

Recent studies involving phototherapy applied prior to exercise have demonstrated positive results regarding the attenuation of muscle fatigue and the expression of biochemical markers associated with recovery. However, a number of factors remain unknown, such as the ideal dose and application parameters, mechanisms of action and long-term effects on muscle recovery. The aims of the proposed project are to evaluate the long-term effects of low-level laser therapy on post-exercise musculoskeletal recovery and identify the best dose andapplication power/irradiation time.

**Design and methods:**

A double-blind, randomized, placebo-controlled clinical trial with be conducted. After fulfilling the eligibility criteria, 28 high-performance athletes will be allocated to four groups of seven volunteers each. In phase 1, the laser power will be 200 mW and different doses will be tested: Group A (2 J), Group B (6 J), Group C (10 J) and Group D (0 J). In phase 2, the best dose obtained in phase 1 will be used with the same distribution of the volunteers, but with different powers: Group A (100 mW), Group B (200 mW), Group C (400 mW) and Group D (0 mW). The isokinetic test will be performed based on maximum voluntary contraction prior to the application of the laser and after the eccentric contraction protocol, which will also be performed using the isokinetic dynamometer. The following variables related to physical performance will be analyzed: peak torque/maximum voluntary contraction, delayed onset muscle soreness (algometer), biochemical markers of muscle damage, inflammation and oxidative stress.

**Discussion:**

Our intention, is to determine optimal laser therapy application parameters capable of slowing down the physiological muscle fatigue process, reducing injuries or micro-injuries in skeletal muscle stemming from physical exertion and accelerating post-exercise muscle recovery. We believe that, unlike drug therapy, LLLT has a biphasic dose–response pattern.

**Trial registration:**

The protocol for this study is registered with the Protocol Registry System, ClinicalTrials.gov identifier NCT01844271.

## Background

Muscle fatigue is a dynamic, time-dependent failure to maintain a desired level of yield or work during a repetitive or sustained activity [1]. Fatigue has a central and peripheral component, both of which affect the production of force during muscle performance. The decline in muscle activity varies in accordance with the type of muscle fiber and intensity of the exercise [2,3]. Fatigue can also contribute to the development of muscle damage, which is characterized by an inflammatory response [4,5], an increase in muscle proteins in the blood [6] and late-onset muscle pain [7-9]. These events occur in a more accentuated fashion when eccentric contractions are employed [6,10,11].

High-performance athletes are prone to muscle damage stemming from training and competition, compromising their performance for a given period of time, which can range from minutes or hours to several days or even months [12]. A large number of therapies are currently employed after sport activities to enhance muscle recovery, such as active recovery [13-15], cryotherapy [9,16], stretching [12] and electrical stimulation [17]. The aim of post-exercise therapy is to reverse muscle damage, with no attempt made to prevent or attenuate the occurrence of muscle damage.

Recent studies by our research group involving low-level laser therapy (LLLT) and LED therapy have demonstrated positive results when applied prior to exercise, with the attenuation of muscle fatigue [18-24] and favoring the recovery of biochemical markers related to muscle damage [25-27]. The findings suggest that LLLT can minimize the occurrence of injury and optimize an athlete’s return to his/her activities in a shorter period of time.

Despite the positive results obtained in the studies cited above, a number of variables remain unknown, such as the ideal dose and application parameters, mechanisms of action and long-term effects on muscle recovery. Based on our line of research, LLLT is a valuable tool for the attenuation of muscle fatigue and the acceleration of post-exercise muscle recovery. As the same biphasic dose–response pattern has been seen in other musculoskeletal disorders and both power and irradiation time exert an influence on the efficacy of therapy, these outcomes justify the development of the proposed study.

## Methods and study design

### Characterization and purpose of study

A double-blind, placebo-controlled, randomized, clinical trial will be carried out in two phases. The study will be conducted at the Laboratory of Phototherapy in Sport and Exercise at Nove de Julho University (UNINOVE) in the city of São Paulo, Brazil. The project has received approval from the Human Research Ethics Committee of the university under protocol number 397774/2011 and the study is supported by a Young Researcher award grant from the Brazilian fostering agency, Sao Paulo Research Foundation (FAPESP), under process number 2010/52404-0.

### Characterization of sample

Twenty-eight male high-level soccer athletes from the same team will participate in each phase of the study. The decision to recruit volunteers from the same team was made to enhance the homogeneity of the sample. For recruitment of volunteers an initial contact will be made with head coaches of several Brazilian soccer teams. If the head coach accepts that the team can be part of the study, then a personal invitation will be made for athletes individually. Afterwards, the research team will ask athletes about their personal data in order to identify if they meet the inclusion criteria or if they need to be excluded from the clinical trial.

### Calculation of sample size

The sample size was calculated based on a previous study [28], in which a similar experimental model and exercise protocol was employed as that to be used in the proposed study. The sample size calculation considered a β of 20% and α of 5%. In the study used as reference for this calculation of Baroni *et al*. [28], LLLT led to the post-exercise recovery of creatine kinase (CK) (muscle injury marker) to 435.95 U/l (standard deviation: 238.04), whereas placebo treatment led to an increase in CK to 1,327.58 ± 949.82 U/l. Using these parameters, a total of seven volunteers would be needed for each of the four groups in each phase of the study (total of 28 volunteers per phase).

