### Composition of groups and randomization process

The volunteers will be randomly allocated to four experimental groups (n = 7 per group) based on the LLLT dose (phase 1) and power (phase 2) (Figure 1). Randomization will be carried out by a simple drawing of lots (A, B, C or D). The laser unit will emit the same sound regardless of the programmed power output. Randomization labels will be created using a randomization table at a central office, where a series of sealed, opaque, numbered envelopes will be used to ensure confidentiality. Randomization will be conducted by a participating researcher, who will have the function of programming the laser device based on the randomization results. This researcher will be instructed not to inform the participants or other researchers regarding the LLLT dose (phase 1) or power (phase 2) until the study has been completed. Thus, the researcher in charge of the administration of the LLLT will be blinded to the dose and power applied to the volunteers.

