### Data analysis

The intention-to-treat analysis will be followed. The primary outcome will be peak torque obtained from MVC at different time-points. Secondary outcomes will be biochemical markers CK, LDH, IL-1β, IL-6, TNF-α, TBARS, carbonylated proteins, CAT and SOD.

Data will be expressed as mean and standard deviation and will be firstly tested regarding normal distribution using Shapiro–Wilk test. ANOVA test with repeated measurements for the time factor will be performed to test between-groups differences (followed by the Bonferroni post hoc test). The level of significance for the statistical analysis will be set at 5% (*P* ≤0.05).

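### On the protocol's own creatine kinase figures, seven athletes per group gives about 60% power rather than the stated 80%, and less once the planned Bonferroni test is applied

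*Protocol article*

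**What the plan says.** The sample size section of the protocol article gives its inputs in full. On error rates: "The sample size calculation considered a β of 20% and α of 5" (per cent), that is, 80% power. On the reference study: "LLLT led to the post-exercise recovery of creatine kinase (CK) (muscle injury marker) to 435.95 U/l (standard deviation: 238.04") and "placebo treatment led to an increase in CK to 1,327.58 ± 949.82 U/l". From these it concludes: "Using these parameters, a total of seven volunteers would be needed for each of the four groups in each phase of the study", or 28 per phase. It names no test, sidedness, scale or pooling rule.

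The Data analysis section plans a repeated-measures ANOVA across the four groups, "followed by the Bonferroni post hoc test", at the 5% level. It does not give the number of post hoc comparisons. It names peak torque as the primary outcome and lists CK among the secondary outcomes.

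**The concern.** A stated result should follow from its stated inputs. Here the standard two-sample calculation does not return seven, and the shortfall is large enough to change how the power statement reads. The calculation also describes a single contrast of laser with placebo at the full 5%, whereas the analysis compares four groups with a multiplicity correction.

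What is at stake is interpretation. A reader told that β is 20% will take a non-significant comparison of a dose with placebo as fair evidence that the dose does not work. At 60% power, an effect as large as the reference study's would be missed 40% of the time, twice the stated rate. After Bonferroni it would be missed more often than found.

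**Working it through.** **Inputs** (all from the sample size section): means 435.95 and 1,327.58 U/l; SDs 238.04 and 949.82 U/l; α 5%; β 20%; seven per group. Two-sided testing is assumed first, since sidedness is not stated.

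**Reproducing the protocol's seven**
- Difference: 1,327.58 − 435.95 = 891.63.
- Arithmetic mean of the SDs: (238.04 + 949.82)/2 = 593.93, so d = 891.63/593.93 = 1.501.
- Two-sided normal formula: n = 2 × (1.960 + 0.842)² / d² = 15.70/2.253 = 6.97, so 7.

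This matches the stated figure exactly. The step is not valid, because the variance of a difference in means depends on the average of the variances, not of the SDs. Even with this SD, t-test power at n = 7 is 73%.

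**With the variances averaged**
- SD = √[(238.04² + 949.82²)/2] = 692.39, so d = 891.63/692.39 = 1.288.
- Two-sided, normal: 15.70/1.658 = 9.47, so 10 per group.
- Two-sided, t test: 11 per group (power 77.7% at 10, 81.9% at 11).
- One-sided, normal: 2 × (1.645 + 0.842)² / 1.658 = 7.46, so 8 per group. One-sided t test: 9 per group.

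**Power at n = 7.** The noncentrality is d × √(7/2) = 1.288 × 1.871 = 2.41.
- Two-sided t test, 12 df: 60.0%. Normal approximation: Φ(2.41 − 1.96) = 67%.
- One-sided: 73.4% (t) or 77.8% (normal).
- Simulation with the two unequal SDs, two-sided: 61% (pooled t) and 54% (Welch).

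**Adding the Bonferroni test** (two-sided, SD 692.39, one dose against placebo). The 12 df column uses two groups' error (2 × 7 − 2); the 24 df column uses four groups' error (4 × 6).

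| Comparisons | α for each | Power at n = 7, 12 df | Power at n = 7, 24 df | n per group for 80% (t test) |
|---|---|---|---|---|
| 3, each dose with placebo | 0.0167 | 39% | 45% | 15 |
| 6, all pairs | 0.0083 | 28% | 34% | 17 |

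**Sensitivity to how many doses work.** Four groups were simulated with the pooled ANOVA error. Each effective dose was given the reference laser mean and SD, and every other group the placebo values.

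| Effective doses | Omnibus F | One effective dose v placebo, 3 comparisons | Same, 6 comparisons |
|---|---|---|---|
| One | 48% | 29% | 19% |
| Two | 74% | 46% | 36% |
| Three | 74% | 69% | 61% |

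No entry reaches 80%.

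**The case against.** The strongest reply is that the article names no test, so other calculations on the same inputs may be meant, and some give seven or fewer.
- **Averaged SDs in the normal formula** give 7. This probably explains the figure but does not justify it.
- **A t test on the log scale** (moments matched to the stated means and SDs) gives 7, with 87% power. This is reasonable for a positive, skewed marker, but the article mentions no log scale and presents the data as means and SDs.
- **The four-group omnibus F formula**, with all three doses fully effective and the variance pooled over groups, gives 6, with 88% power at 7. Simulating that case with the unequal SDs lowers the power at 7 to about 74%.
- **An unadjusted pairwise test** with pooled four-group error and all three doses effective reaches 80%. With these unequal SDs its type I error is about 16%, and it is not the planned Bonferroni analysis.

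What stands is that a reader should not infer that every possible calculation needs at least eight per group. What does not stand is the rescue of the stated figure: each route rests on an invalid step or on a choice the article does not state.

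A second fair reply is that a single post-Bonferroni figure of about 30% would be too definite. It presumes all six pairs, which the article does not specify, so only a range can be given.

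A reader might also infer that an underpowered CK test decides which dose goes into phase 2. The text does not support this. The section on phase 2 carries forward the dose with the best phase 1 results and mentions no significance test, and CK is only a secondary outcome.

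**Conclusion.** The point holds for the stated sample size and power. On the article's own inputs, a two-sided comparison of one dose with placebo needs 10 (normal) or 11 (t test) per group, and seven gives about 60% power. One-sided testing does not close the gap (about 73% by t test). After Bonferroni, power is about 39–45% for three comparisons or 28–34% for six.

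These figures assume that a single dose has the full reference effect, that CK is analysed untransformed, and that the variances are averaged to an SD of 692.39. The post-Bonferroni figures also depend on how many doses work: the simulations run from 19% to 69%. All are powers for CK. They say nothing about power for peak torque, for which the article gives no calculation.

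**What to change.** Keep seven per group and replace the concluding sentence of the sample size section with wording such as:

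> With 7 per group, power to detect the reference CK difference for one dose versus placebo is about 60% (two-sided 5%, t test), and about 28–45% after Bonferroni depending on whether six or three comparisons are made; 80% unadjusted power would need 11 per group. This is power for CK, a secondary outcome, and not for the primary outcome, peak torque. Non-significant pairwise dose comparisons will be treated as inconclusive.

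State the pooled SD (692.39) beside it so that the figure can be checked. If the number of post hoc comparisons is settled elsewhere, give the matching part of the range.

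The cost is one reworded paragraph and a less favourable power statement. No extra athletes are required, and the design and analysis do not change.

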### Inclusion criteria

The following inclusion criteria will be employed:

•Professional soccer athletes;

•Age between 18 and 35 years;

•Male gender;

•Minimum of 80% participation in team practice sessions;

•Light or intermediate skin color [29];

•Agreement to participate through signed statement of informed consent.

### Exclusion criteria

Participants with the following will be excluded from the study:

•History of musculoskeletal injury to hips or knees in the previous 2 months;

•Use of pharmacological agents or nutritional supplements;

•Occurrence of musculoskeletal injury during the study;

•Any change in practice routine in relation to the rest of the team during the study.

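### Two exclusion criteria can remove athletes after randomisation, and the article does not reconcile them with its intention-to-treat analysis

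*Protocol article*

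**What the plan says.** The Exclusion criteria section opens with "Participants with the following will be excluded from the study" and lists four items. Two describe events in the course of the trial: "Occurrence of musculoskeletal injury during the study" and "Any change in practice routine in relation to the rest of the team during the study".

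Under Composition of groups and randomization process, "The volunteers will be randomly allocated to four experimental groups (n = 7 per group"). The allocated laser or placebo application, the eccentric exercise and measurements up to 96 hours follow.

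The Data analysis section states "The intention-to-treat analysis will be followed", with peak torque from the MVC test as primary outcome and a repeated-measures ANOVA. The article does not say what happens to the data of an athlete who meets one of the two items after allocation.

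The Discussion paragraph of the abstract, and the Discussion itself, name "reducing injuries or micro-injuries in skeletal muscle stemming from physical exertion" among the effects that the laser parameters are sought for.

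**The concern.** An intention-to-treat analysis keeps each randomised athlete in his allocated group whatever happens later. A rule that takes athletes out of the study for later events does the opposite if it also takes them out of the analysis. The article states both rules, so this is a conflict in the text and not a detail left to a fuller document. It leaves the analysis set open to be settled after the data are seen.

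Such losses need not be random. Muscle injury from exertion is close to what the laser is meant to reduce. An athlete who recovers slowly might also train differently from his team, although the article does not say so. If either event depends on the athlete's recovery or on his treatment, the athletes who remain are no longer the groups that randomisation formed. Blinding does not protect against this, because the exclusion follows from the athlete's condition.

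Two features raise the stakes. The groups have 7 athletes each. The dose judged best in phase 1 is carried into phase 2, so a distorted arm in phase 1 could affect the whole of phase 2.

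**Working it through.** **1. The passages side by side**

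| Question | Exclusion criteria | Data analysis |
|---|---|---|
| Who is affected? | Athletes injured or with a changed routine during the study | All randomised athletes |
| What happens? | Excluded from the study | Intention-to-treat |
| Are data kept? | Not stated | Implied by the term, not spelled out |

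The study runs from enrolment through randomisation and treatment to 96 hours after exercise, so both events can fall before or after allocation. Only those after allocation create the conflict.

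**2. Is there any reserve?** Calculation of sample size uses creatine kinase: mean 435.95 (SD 238.04) U/l with laser and 1,327.58 (SD 949.82) U/l with placebo, α 5%, β 20%. Sidedness is not stated; two-sided is assumed here.

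- Difference: 1,327.58 − 435.95 = 891.63.
- Simple mean of the two SDs: (238.04 + 949.82)/2 = 593.93.
- n per group = 2 × [593.93 × (1.960 + 0.842)/891.63]² = 6.97, so 7.

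This reproduces the stated 7 exactly, and 7 is also the number randomised, so no reserve for losses is built in. With the root-mean-square SD (692.39) the same formula gives 9.47, so 10; on that basis there is even less room.

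Power for this creatine kinase comparison is Φ[891.63/(SD × √(2/n)) − 1.960], with two groups of equal size n:

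| n per group | SD 593.93 | SD 692.39 |
|---|---|---|
| 7 | 80.2% | 67.3% |
| 6 | 73.9% | 60.7% |
| 5 | 66.0% | 53.0% |

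These figures do not describe power for peak torque, the primary outcome.

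**3. How likely is at least one exclusion?** The article gives no rate. For an assumed rate p per athlete, the chance of at least one exclusion among the 28 in a phase is 1 − (1 − p)²⁸, and the expected number is 28p.

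| Assumed p | At least one | Expected number |
|---|---|---|
| 2% | 43% | 0.6 |
| 5% | 76% | 1.4 |
| 10% | 95% | 2.8 |

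**4. What could one outcome-related exclusion do?** Assume a normal outcome and the loss of exactly the worst athlete from one group of 7.

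- Share of the arm: 1/7 = 14.3%.
- The expected lowest of 7 standard normal values is −1.352. Removing it moves the mean of the other six by 1.352/6 = 0.225 SD.
- The group's SD falls to about 0.83 of its full value (simulation).
- With no true effect, a two-sided t-test against an intact group of 7 has a type I error of 7.7% instead of 5.0%. If the two worst are lost, the shift is 0.42 SD and the error 11.8% (simulation).
- With a true benefit of 1.2 SD, losing the worst placebo athlete reduces the expected difference to 1.2 − 0.225 = 0.975 SD, and power falls from 54% to 41% (simulation). Losing the worst laser athlete instead raises the expected difference to 1.2 + 0.225 = 1.425 SD.

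The sign of the bias therefore depends on which arm loses the athlete. The article does not allow that to be predicted.

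**The case against.** The strongest reply is that the two sections govern different things. Exclusion may mean withdrawal from further procedures, with the data already collected kept in the allocated group, which is compatible with intention-to-treat. This stands to the extent that the two rules are not impossible to follow together. It does not remove the point: the text says excluded from the study, and nothing in the article supplies the milder meaning.

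A reader might infer that both items necessarily act after randomisation. The wording also covers the time between enrolment and allocation, when excluding an athlete breaches nothing.

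A reader might also infer that the exclusions are known to depend on outcome and would pull the laser effect towards zero. The article does not support this. The injuries named in the treatment aim are exertional and include micro-injuries, and the exercise is meant to induce muscle damage. The exclusion item speaks of musculoskeletal injury, which may mean an unrelated injury, for example one from football. The routine item may simply hold training load constant within one team. Overlap with outcome is possible, not established. A shift towards zero would need more exclusions from placebo, and the smaller SD partly offsets that shift in a test statistic. Nor does the article say that excluded injuries would go unreported, so it cannot be claimed that harm would be hidden.

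Finally, striking out the injury item would remove the only text on an athlete injured during the study. That objection stands, and the remedy has to respect it.

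**Conclusion.** The point holds as a conflict between two stated rules. Read literally, the exclusion criteria can take randomised athletes out of a trial that declares intention-to-treat, and no section reconciles the two. Bias is possible because the reasons for exclusion may be related to outcome or treatment. Its direction and size cannot be calculated from the article.

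The shift of about 0.23 SD is an illustration. It rests on a normal outcome and on the loss of exactly the worst athlete from one group; the exclusion rates of 2% to 10% are likewise assumed. What needs no assumption is that one exclusion removes 14% of an arm and that no allowance for losses is stated. The analysis set should be settled before any outcome data are examined.

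**What to change.** Reconcile the Exclusion criteria with the Data analysis section as follows.

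- Apply the two items as exclusion criteria only up to randomisation.
- After randomisation, record both as events, by arm and with their timing, and state that they do not remove an athlete from the analysis.
- State separately whether an affected athlete continues study procedures. This is a clinical decision, which the analysis rule should neither make nor depend on.
- Analyse every randomised athlete in his allocated group with all values obtained, using a likelihood-based mixed model for repeated measures so that a missed visit does not drop the athlete.
- Report the analysis without affected athletes only as a labelled sensitivity analysis.

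The cost is a few sentences of protocol text, replacement of the repeated-measures ANOVA by the mixed model, one extra analysis, and slightly more variability from the athletes kept in.
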